#### Passive Oddball Paradigm

Emotional and neutral words uttered by human voices recorded in stage 1 and synthesized voices created in stage 2 will be displayed to the participant. During the EEG recording, participants will sit on an armchair while watching a silent movie and will be instructed to pay no attention to the auditive stimuli. To facilitate the comparison of naturalness levels, six stimulus blocks will be created, each containing 600 stimuli corresponding to one of the five levels, or the human voice. Each block will consist of 480 frequently presented neutral-uttered standard stimuli (80%), and occasional 24 anger (4%), 24 disgust (4%), 24 fear (4%), 24 happiness (4%), and 24 sadness (4%) deviant stimuli. Standard and deviant stimuli will be equally uttered with a male, woman, or child voice. The stimuli will be presented pseudo-randomly with deviant stimuli being preceded by at least two standard stimuli. Each participant will listen to three blocks for an approximatively 30-min task. The stimulus sequences for each block will be fixed, and the order of blocks will be counterbalanced and randomized between participants. The stimulus onset asynchrony will be of 1,300 ms. The stimuli will be presented at 60 dB via the Shure SRH1840 audio headset that has a flat response frequency response in order to accurately reproduce the input audio signal. Autistic participants will be accompanied by their parent if necessary.

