##### Statistical analysis

The statistical significance of ERP components will be tested by comparing their mean amplitudes to zero at ROIs using one-sample t-tests. This method will allow us to focus exclusively on significant responses, and to distinguish significant scalp distributions from noise. Statistically significant ERPs will be considered for further amplitude analysis.

For standard stimuli, levels of naturalness comparisons will be performed by Level × ROI repeated measures ANOVAs on each ERP and group independently. For deviant stimuli, Level × ROI × Deviant repeated measures ANOVAs will be performed.

Group comparisons will be conducted by Group × ROI repeated measures ANOVAs on each ERP and level of naturalness separately, for standard stimuli. Similarly, for deviant stimuli, Group × ROI × Deviant repeated measures ANOVAs will be performed. The effect of reducing the naturalness of voice on emotion processing will be assessed by the comparison between ERPs amplitudes at levels 1–5 for ASD group and ERPs amplitudes calculated in the control group for human voices. We expect to detect less natural voices to help typical processing in ASD children, that is, fewer difference with non-pathological processing of human voices at least natural voices. Based on MMN analysis at maximum peak ROI, the voice leading to the nearest to non-pathological processing in autistic children will be chosen for Stage 3.

Scalp distribution comparisons for standard stimuli will be assessed by Group × Laterality (FP1, F3, F7, T7, C3, P3, P7, O1/AFz, Fz, CPz, Cz, POz, Pz/FP2, F4, F8, T8, C4, P4, P8, O2) repeated measures ANOVAs on each ERP and level of naturalness separately. For deviant stimuli, Group × Laterality × Deviant repeated measures ANOVAs will be conducted.

For all amplitude analysis, normality will be assessed by Shapiro–Wilk test. In case of non-parametric distribution of the data, a transformation will be applied. Mauchly’s test of sphericity will be used to evaluate homogeneity of variances and co-variances. In case of violation of sphericity, a Greenhouse-Geisser correction will be applied in order to test main effects significance. *Post hoc* comparisons will be conducted to assess specific differences (Tukey and Dunnett procedures). In all cases, level of significance will be set at *p* < 0.05 and statistical analysis will be performed with R software.

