#### Participants

Typically developed participants will be recruited from a public announcement posted on Tecnologico de Monterrey, Campus Monterrey. Autistic participants will be recruited by contacting parents of autistic children attending San Jose Hospital from Tecnologico de Monterrey.

Sample size estimation was calculated with G^∗^Power software version 3.1.9.7 (Faul et al., 2007) for Cohen’s d effect size index of 0.8, correlations among repeated measures of 0.5, statistical significance set at *p* < 0.05. For level comparisons, results indicated that 20 participants in each group would be enough to provide an estimated power of 0.90. For group comparisons, results indicated that 38 participants in each group would be enough to provide an estimated power of 0.91.

Forty high-functioning autistic volunteers aged 9 to 11-year-old will be involved in this stage of the research. All autistic participants will be diagnosed by a clinician according to DSM-V (Diagnostic and Statistical Manual of Mental Disorders, Fifth Edition) (American Psychiatric Association, 2013) or the International Classification of Diseases and Related Health Problems – Tenth Edition (World Health Organization, 1994) criteria. Autistic symptomatology will be assessed by the Autism Spectrum Rating Scales (ASRS) – parent report (Goldstein, 2012). A T-score greater than 60 (slightly elevated to very elevated scores for autistic behaviors) on Social/Communication, DSM-IV-TR (Text Revision), Peer and Adult Socialization and Social/Emotional Reciprocity domains will be considered as an inclusion criterion.

In addition, 40 TD volunteers aged 9 to 11-year-old will be included in this study. Similar to autistic children, ASRS will be used, and children with a score inferior to 60 in all scales will be included.

Any TD or autistic participant will be excluded if child:

•is under medication affecting the central or peripherical nervous system,•has hearing loss or deficits, and/or•has history of a developmental pathology and/or any disease affecting behavior and nervous system, apart from ASD for autistic participants.

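### Stage 2 gives each child three of the six voice blocks but compares levels by repeated-measures ANOVA, which does not fit this incomplete-block design; a mixed model with a child effect and a stated triplet allocation would.

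*Protocol article*

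**What the plan says.** All places are in Stage 2 of the protocol article.

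- *Passive Oddball Paradigm*, conditions: "six stimulus blocks will be created, each containing 600 stimuli corresponding to one of the five levels, or the human voice".
- Same section, exposure: "Each participant will listen to three blocks for an approximatively 30-min task". On allocation it says only that "the order of blocks will be counterbalanced and randomized between participants". No rule is given for which three blocks a child hears.
- *Statistical analysis*, standard stimuli: "levels of naturalness comparisons will be performed by Level × ROI repeated measures ANOVAs on each ERP and group independently". Deviant stimuli get the same analysis with Deviant as a further factor. Mauchly's test and, if needed, a Greenhouse-Geisser correction follow. No mixed or incomplete-block model is named.
- *Statistical analysis*, voice choice: autistic children's amplitudes at levels 1–5 are set against the controls' amplitudes for human voices and, from the MMN at the maximum-peak ROI, "the voice leading to the nearest to non-pathological processing in autistic children will be chosen for Stage 3".
- *Participants*: d = 0.8, correlation among repeated measures 0.5, alpha 0.05. "For level comparisons, results indicated that 20 participants in each group would be enough to provide an estimated power of 0.90". For group comparisons the figure is 38 per group at power 0.91. Forty autistic and 40 typically developed (TD) children are planned.

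**The concern.** The design and the named test do not fit each other. A child supplies three of six levels, so Level is partly crossed with child: the levels a child hears share that child's overall amplitude, and the levels a child does not hear are missing by design. A classical repeated-measures ANOVA on Level, with its sphericity test, needs every level from every child. Treating Level as a between-child factor runs, but ignores that the three blocks come from one child.

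At stake is the efficiency and calibration of the within-group comparison of naturalness levels, which is Stage 2's direct test of whether reducing naturalness changes emotional processing. Allocation also matters. If the triplets are not planned, some pairs of levels may be compared within few children, and that cannot be repaired once the EEG has been recorded.

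**Working it through.** **1. Complete cases.** Six conditions, three per child. Children with all six levels: 0 of 40 per group. If the human voice is left out and Level has five values, the count is still 0.

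**2. Exposure under even allocation (assumed, not stated).** 40 × 3 / 6 = 20 children per level in each group. There are 20 possible triplets of six levels. Using each twice fills 40 children, and each pair of levels then occurs together in 40 × 3 / 15 = 8 children.

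**3. Reproducing the stated sample size.** Inputs: f = d/2 = 0.4, ρ = 0.5, m = 18 ROIs (counted from the list in the Stage 2 *Data Analysis* section), alpha 0.05. Reading d = 0.8 as f = 0.4 is supported elsewhere in the article: 19 words in each of six emotions gives 0.916 (stated 0.92).

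Formula (repeated measures, between factors): λ = f²·N·m / (1 + (m − 1)ρ), with df k − 1 and N − k.

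- Level, k = 6 with 10 children each: λ = 0.16 × 60 × 18 / 9.5 = 18.19, df 5 and 54, power **0.899** (stated 0.90). Children needed at three blocks each: 10 × 6 / 3 = **20**, as stated.
- Group, k = 2 with 19 each: λ = 0.16 × 38 × 18 / 9.5 = 11.52, df 1 and 36, power **0.910** (stated 0.91). At half exposure: 19 × 6 / 3 = **38**, as stated.

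Other readings of the 20 that were tried do not return 0.90:

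| Reading | Power |
|---|---|
| Six levels between children, 20 per level | 0.999 |
| Six levels within child, complete, N = 20 | 0.999 |
| Five levels between children, 10 per level | 0.857 |

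So the level figure matches a calculation in which each child's three blocks are three separate subjects.

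**4. What that reading costs.** Simulation with 40 children, all 20 triplets twice, one amplitude per block, total SD 1, ρ = 0.5. The F test for Level is computed without child effects (df 5 and 114) and with them (df 5 and 75).

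| Level effect | Blocks as independent | With child effect |
|---|---|---|
| None (type I error) | 0.015–0.019 | 0.05 |
| f = 0.4 (protocol) | about 0.94 | 0.99 |
| f = 0.25 (assumed) | 0.46 | 0.73 |

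Range and rounding reflect repeated runs of 4,000 to 20,000 simulations.

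Analytic check of the right-hand column: design efficiency E = 6 × 2 / (3 × 5) = 0.80 and λ = E × 20 × 6 × f² / (1 − ρ). At f = 0.4, λ = 30.72 and power is 0.994. At f = 0.25, λ = 12.0 and power is 0.73. With only the stated 20 children per group and f = 0.4, λ = 15.36 and power is 0.81.

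**5. Group comparisons at one level.** These use different children in each group and are not affected. With 20 v 20, λ = 12.13 and power is 0.92.

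**The case against.** **The label may be loose.** The same section calls Group × ROI a repeated-measures ANOVA although Group is between children, so ROI alone may be the repeated factor. This stands: the wording does not prove that a complete within-child analysis was meant. But the remaining reading is then the one that ignores the child. A third option, an ANOVA with child as block, runs on three-of-six data. It is not what is described, and the Mauchly and Greenhouse-Geisser steps do not fit it.

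**The loss is small on the protocol's own terms.** This also stands. At f = 0.4 the planned 40 per group have ample power either way; the larger gap appears only at f = 0.25, which is an assumption.

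**An article may leave model detail to a fuller plan.** True of detail, but here the article fixes both the exposure and a test that does not match it.

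Four stronger inferences are not supported:

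- *That the misfitting ANOVA selects the Stage 3 voice.* The selection rule is a separate, between-group comparison: autistic children at levels 1–5 against TD children hearing the human voice. A conservative Level test does not itself change which voice comes out nearest.
- *That false positives are inflated.* The error runs the other way.
- *That the sample is too small.* A child-effect analysis of 40 children has power 0.99 at f = 0.4.
- *That only 20 of 40 TD children will hear the human voice.* Twenty follows from even allocation, which the sample-size arithmetic suggests but the text does not state.

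**Conclusion.** The point holds as a mismatch between design and analysis. As a within-child factor, Level cannot be tested by the named ANOVA because no child is complete. As a between-child factor, which the stated 20 at 0.90 implies, the test treats correlated blocks as independent. The consequence is lost efficiency and a miscalibrated test: true alpha about 2% instead of 5%, and power about 0.94 instead of 0.99 at f = 0.4, or 0.46 instead of 0.73 at f = 0.25.

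These figures assume 40 children per group, balanced triplets, one amplitude per block and correlation 0.5. The sample size need not change. The stated 20 per group rests on an independence calculation; under an incomplete-block analysis, 20 children would give 0.81, and it is the planned 40 that secures the comparison.

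**What to change.** 1. **Model.** Replace the Level × ROI (× Deviant) ANOVAs by a linear mixed model with a child random effect and Level, ROI and Deviant (with interactions) as fixed effects. Add a random term for block within child, because ROIs and deviants recorded in one block share error. All three blocks of every child are then used, and the Mauchly and Greenhouse-Geisser steps fall away for Level.
2. **Allocation.** State which triplets are used, so that each pair of levels occurs equally often within each group, for example all 20 triplets twice per group of 40. Keep the randomised block order.
3. **Sample size.** Restate the basis of the level-comparison figure to match this analysis.

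The cost is revised analysis wording and a block list fixed before recording. No extra children or session time are needed. Having each child hear all six blocks would also restore the ANOVA, but would take 6 × 600 × 1.3 s = 78 min.

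**Optional trade-off.** Giving every TD child the human block would raise the reference used for the voice choice from 20 children (if allocation were otherwise even) to 40. For one autistic level against TD human at d = 0.8, as a single-measure t test, power rises from 0.69 (20 v 20) to 0.82 (20 v 40). The price is 40 × 2 / 5 = 16 instead of 20 TD children per synthetic level. Same-level group tests fall from 0.92 to 0.89 by the protocol's method, below the stated 0.91. Equal pair frequency is also lost in the TD group: each human–level pair occurs 16 times and each level–level pair 4 times. It should be a deliberate choice, not part of the core correction.

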#### EEG Recording and Processing

Electroencephalographic signals will be recorded with a 10/20 International System with 24 channels (Greentek Gelfree S3, mBrain Train) with a sampling rate of 500 Hz into a bandwidth between 0.1 and 100 Hz. EEG Lab toolbox from Matlab will be used to preprocess and process the data. Before data analysis, the signal will be referenced to the average between left and right mastoids. Electrode impedance will be kept below 5 kΩ. EEG data will be epoched over a window time of 1,100 ms, including a pre-stimulus 100 ms for baseline correction. A High-pass filter of 0.1 Hz and a low-pass filter of 50 Hz will be applied before epoching. The removal of eye movements and muscle artifacts will be based on the independent component analysis method using the ICLabels plug-in of EEG Lab. Epochs with a voltage exceeding 100 μV will be removed from data analysis.

#### Data Analysis

For ERP amplitude analysis, electrodes will be grouped according to regions of interest (ROIs). Left prefrontal site: FP1. Left frontal channels: F3, F7. Right prefrontal site: FP2. Midline pre-frontal site: AFz. Midline frontal electrode: Fz. Right frontal channels: F4, F8. Left temporal site: T7. Left central electrode: C3. Midline central electrode: Cz. Right temporal site: T8, Right central electrode: C4. Centro-parietal electrode: CPz. Left parietal sites: P3, P7. Midline-parietal electrode: Pz. Right parietal sites: P4, P8. Midline parieto-occipital electrode: POz. Left occipital site: O1. Right occipital site: O2. Maximum peak time window analysis will be: 100–250 ms for the MMN (Kujala et al., 2007; Paris et al., 2018), 170–230 ms for P200 component (Paulmann et al., 2013), 200 and 350 ms for the P3a (Kujala et al., 2007; Paris et al., 2018), and 400–1,000 ms for the LPP component (Steber et al., 2020).

Event-Related Potentials will be extracted by averaging the data obtained for standard and deviant stimuli, and for each condition independently. The ERPs elicited by standard stimuli will be subtracted from the ERPs elicited by deviants to calculate difference waves. The mean ERPs amplitude will be calculated as follows. For standard stimuli, level of naturalness and group average peak latencies will be determined from all ROIs. Mean amplitudes will be determined by considering a ±50-ms time window centered at the grand mean peak latency. For deviant stimuli, mean amplitudes will be calculated from the difference waves at ROIs. Mean amplitudes will be determined by considering a ±50-ms time window centered to the grand mean peak latency (Kujala et al., 2007; Paris et al., 2018).

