##### EEG assessments

After behavioral assessment at pre- (1st session), mid- (7th session), end- (13rd session), and follow-up sessions (2 and 6 weeks after the end of the intervention), EEG data will be recorded while participants listen to a passive oddball paradigm. Emotional and neutral words uttered by human voices recorded at Stage 1 will be displayed to the participant. During the EEG recording, participants will sit on an armchair while watching a silent movie and will be instructed to pay no attention to the auditive stimuli. One stimulus block containing 1,200 words will be presented for an approximately 20-min paradigm. It will consist of 960 frequently presented neutral-uttered standard stimuli (80%), and occasional 48 anger (4%), 48 disgust (4%), 48 fear (4%), 48 happiness (4%), and 48 sadness (4%) deviant stimuli. Standard and deviant stimuli will be equally uttered with a male, woman, or child voice. The stimuli will be presented pseudo-randomly with deviant stimuli being preceded by at least two standard stimuli. The stimulus sequence will not vary between participants. The stimulus onset asynchrony will be of 1,300 ms. The stimuli will be presented at 60 dB via the Shure SRH1840 audio headset. Autistic participants will be accompanied by their parent if necessary.

Electroencephalographic recording and processing will follow the same methodology as the one described in section “EEG Recording and Processing.”

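### The standard ERP is averaged with no stated exclusion of the roughly 25% of standards that directly follow an emotional deviant; this could attenuate the difference waves by up to 25%, and excluding them costs 0.8% in precision per emotion.

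*Protocol article*

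**What the plan says.** The Stage 2 section Passive Oddball Paradigm sets 600 stimuli per block: 480 neutral standards, and "occasional 24 anger (4%), 24 disgust (4%), 24 fear (4%), 24 happiness (4%), and 24 sadness (4%) deviant stimuli". The order is constrained by one rule: "The stimuli will be presented pseudo-randomly with deviant stimuli being preceded by at least two standard stimuli". Voices are mixed: "Standard and deviant stimuli will be equally uttered with a male, woman, or child voice". The Stage 3 section EEG assessments doubles the counts to 960 standards and 48 deviants of each of five emotions, under the same ordering rule and voice mix.

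The averaging rule stands in Data Analysis (Stage 2) and is repeated in ERPs (Stage 3): "Event-Related Potentials will be extracted by averaging the data obtained for standard and deviant stimuli, and for each condition independently", followed by "The ERPs elicited by standard stimuli will be subtracted from the ERPs elicited by deviants to calculate difference waves". The only epoch exclusion given is the 100 μV limit in EEG Recording and Processing, which also applies in Stage 3.

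The mean amplitudes are first tested against zero at each region of interest, and only significant components go on to further analysis. In Stage 2 the MMN at the region with the largest peak decides which synthesized voice is used in Stage 3.

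**The concern.** The ordering rule controls what comes before a deviant, but nothing is said about the standard that comes after one. That standard is a switch from emotional back to neutral prosody and may evoke a change response of its own. If it does, averaging it with the other standards and subtracting the result removes part of the change response from itself. The effect is one-sided, because no deviant ever follows a deviant.

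At stake are the size of the MMN and P3a, the chance that a real component passes the screening test against zero, and possibly the comparison that selects the Stage 3 voice.

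**Working it through.** **Inputs from the protocol article.** Stage 2 block: 480 standards and 5 × 24 = 120 deviants. Stage 3 block: 960 standards and 5 × 48 = 240 deviants. At least two standards stand before each deviant.

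**Assumed input.** r is the response to a post-deviant standard as a fraction of the full change response M. The documents give no value; the range used is 0 to 1.

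**1. Block composition.** 480/600 = 960/1,200 = 80% standards, and 24/600 = 48/1,200 = 4% per emotion. The stated percentages reproduce.

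**2. Share of post-deviant standards.** Two deviants can never be adjacent, so every deviant is followed by a standard unless it ends the block.
- Stage 2: 119 or 120 of 480 = 24.8% to 25.0%.
- Stage 3: 239 or 240 of 960 = 24.9% to 25.0%.

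These counts are before artefact rejection; the share is unchanged if rejection is equally frequent in both kinds of standard.

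**3. Effect on the difference wave.** Let S be the response to an undisturbed standard. The deviant average is S + M. The standard average is S + 0.25rM. The difference is M(1 − 0.25r).

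| r (assumed) | Multiplier | Loss |
|---|---|---|
| 0 | 1.000 | 0% |
| 0.25 | 0.9375 | 6% |
| 0.5 | 0.875 | 12.5% |
| 1 | 0.750 | 25% |

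**4. Precision given up by excluding them.** With equal single-trial variance, the trial-noise standard error of a difference wave is proportional to √(1/n_deviant + 1/n_standard).
- One emotion, Stage 2: √[(1/24 + 1/360)/(1/24 + 1/480)] = 1.008, a rise of 0.8%. Stage 3 has twice as many of each, so the ratio is the same.
- Five emotions pooled: √[(1/120 + 1/360)/(1/120 + 1/480)] = 1.033, a rise of 3.3%.
- Standard average alone: √(480/360) = 1.155, a rise of about 15%.

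**5. Break-even.** Exclusion improves the ratio of signal to trial noise once 1/(1 − 0.25r) exceeds the standard-error ratio. For one emotion this is r above (1 − 1/1.0079)/0.25 = 0.03. Pooled, it is r above (1 − 1/1.0328)/0.25 = 0.13.

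**6. Voice selection.** Let A be the autistic group's MMN at a given level and T the control MMN for human voice. If r is common to all groups and levels, each distance |A − T| becomes (1 − 0.25r)|A − T|, and the order of the voices is unchanged. If r differs by group or level, A and T carry different multipliers and the order can change.

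**The case against.** **The article does not say that all standards are used.** True; it is silent, and a condensed article may leave trial selection to a fuller plan. But the text gives an averaging rule with a single named exclusion, alongside regions, windows, filters and baseline. Followed as written, it keeps the post-deviant standards. The point is offered as a cheap improvement to that stated rule.

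**The harm rests on r.** This stands. A neutral word after one emotional word returns to the 80% background, so r near 1 is an extreme, and r = 0 is possible. A reader might infer that the MMN will be understated; the documents support only that it could be.

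**Power.** A reader might apply the multiplier to the planned d = 0.8. At the protocol's 38 per group, a two-sample t-test would then fall from 0.93 to 0.90, 0.85 or 0.73 at r = 0.25, 0.5 or 1. That is a worst case, because it holds the between-child SD fixed. If each child's wave is scaled, the true spread between children shrinks too, and if that were all of the SD, d would not change. No particular power loss is established.

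**Wrong voice chosen.** A reader might infer this, since the MMN selects the voice. Step 6 shows that it needs r to differ by group or level, and nothing in the documents shows that it does.

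**Baseline carry-over.** With a 1,300 ms onset asynchrony and a 100 ms baseline, the post-deviant standard's baseline lies 1,200 to 1,300 ms after the emotional word's onset. The stated LPP window ends at 1,000 ms, and no carry-over figure is given, so this adds nothing firm.

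**The remaining background is not constant.** This stands. Standards are shared equally among three voices. If voice order is random (an assumption), about two-thirds of standards follow a different voice. Exclusion removes the one-sided emotional change but not this variation.

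**Conclusion.** The point holds as a possible attenuation that is cheap to avoid. That about 25% of standards directly follow a deviant, in both stages, follows exactly from the design. The loss in the difference wave is 0.25r, between 0% and 25%, and r is unknown. This can understate the MMN and P3a and make components less likely to survive the screen against zero. Keeping these standards buys little: a trial-noise standard error 0.8% smaller per emotion. Under equal single-trial variance, exclusion pays for a single emotion at any r above about 0.03. The conclusion takes the averaging rule as written and does not rest on any claim about power or about the voice finally selected.

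**What to change.** In Data Analysis (Stage 2) and ERPs (Stage 3), state that the standard ERP used for the difference waves leaves out the first standard after each deviant. About 360 standards per Stage 2 block and 720 in Stage 3 remain before artefact rejection.

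This is a change in trial selection at the analysis step, with no extra recording. The price is the 0.8% (single emotion) or 3.3% (pooled) wider trial-noise standard error. Say separately whether the same exclusion applies to the analyses of standard stimuli alone. There it would remove the same possible change response, but it raises the trial noise of the standard average by about 15%, so it is a real trade-off and should be decided in advance.

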### EEG Signature of Emotion Recognition

To record the brain signature of emotions differentiation in voice, soundless methods may be more suitable since the recording process does not interfere with the acoustic stimulus that has to be processed. EEG, and particularly the analysis of Event-Related Potentials (ERPs), has been widely used to study the neuronal activation process of emotions. Furthermore, thanks to its high temporal resolution, ERPs analysis enable the distinction within attentional, sensory, and higher cognitive stages (Fan and Cheng, 2014). Early automatic auditory perception is usually observed between 100 and 250 ms over frontal and central cortices after stimulus onset (MMN). Higher amplitude of this component indicates higher discrimination of acoustic modulations relative to constant auditory background (Charpentier et al., 2018). As an index of acoustic changes early discrimination, the MMN can be used as an indicator of emotional prosody detection (Lindström et al., 2016, 2018; Paris et al., 2018). If automatic changes discrimination was salient enough, involuntary attentional switch to deviant auditory stimuli happens, and is observed 200–350 ms after stimulus onset at fronto-central cortices as a component known as P3a (Lindström et al., 2018; Paris et al., 2018). Early emotional recognition, valence, and arousal identification appear over frontal and central electrodes between 250 and 350 ms after the stimulus onset (Paulmann et al., 2013). The analysis of the amplitude of the P200 component has allowed to distinguish different prosodies such as disgust (high amplitude) and fear (lower amplitude) (Paulmann et al., 2013). This component has shown to reflect the early arousal decoding and may predict the deeper processing of the emotional information observed in the 250–1,000 ms time-window after the stimulus onset (Paulmann, 2016; Steber et al., 2020). The time window between 400 and 1,000 ms has been related to the motivational relevance and extensive processing of the prosodic emotional stimulus. In such window, the observation of the Late Positive Potential (LPP) over centro-parietal recording sites is frequent (Steber et al., 2020). The LPP amplitude is higher in emotional than neutral stimuli, while it is shorter during the emotional down-regulation (Pan et al., 2020).

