##### ERPs

For ERP amplitude analysis, electrodes will be grouped according to ROIs described in section “Data Analysis.” Maximum peak time windows used for data analysis of ERPs will be identical to the one mentioned in section “Data Analysis.” MMN, P200, P3a, LPP will be under study.

Event-Related Potentials will be extracted by averaging the data obtained for standard and deviant stimuli, and for each condition independently. The ERPs elicited by standard stimuli will be subtracted from the ERPs elicited by deviants to calculate difference waves. The mean ERP amplitude will be calculated as follows. For standard stimuli, group and assessment session average peak latencies will be determined from all ROIs for TD and ASD separately. Mean amplitudes will be determined by considering a ±50-ms time window centered to the grand mean peak latency. For deviant stimuli, mean amplitudes will be calculated from the difference waves at ROIs. Mean amplitudes will be determined by considering a ±50-ms time window centered to the grand mean peak latency (Kujala et al., 2007; Paris et al., 2018).

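### The LPP is scored with a peak-centred ±50 ms rule that cannot be completed for peaks after 950 ms and, for standard stimuli, may be placed differently in the conditions being compared

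*Protocol article*

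**What the plan says.** The Introduction (EEG Signature of Emotion Recognition) treats the late window as one of prolonged processing: "The time window between 400 and 1,000 ms has been related to the motivational relevance and extensive processing of the prosodic emotional stimulus".

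The Stage 2 Data Analysis section then lists windows in which a peak is to be found. The list opens with "Maximum peak time window analysis will be: 100–250 ms for the MMN" and closes with "400–1,000 ms for the LPP component". One scoring rule follows for all components. For standard stimuli, "level of naturalness and group average peak latencies will be determined from all ROIs", and then: "Mean amplitudes will be determined by considering a ±50-ms time window centered at the grand mean peak latency". For the others, "For deviant stimuli, mean amplitudes will be calculated from the difference waves at ROIs", again over ±50 ms, without saying which average supplies the latency.

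The Stage 3 ERPs section keeps the same windows and the same rule. For standard stimuli it states that "group and assessment session average peak latencies will be determined from all ROIs for TD and ASD separately".

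On epoch length, EEG Recording and Processing says: "EEG data will be epoched over a window time of 1,100 ms, including a pre-stimulus 100 ms for baseline correction".

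In both stages the amplitudes are first tested against zero with one-sample t-tests, and only significant components go on to the Level, Group and Session analyses. No exception is made for the LPP and no rule is given for late peaks.

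**The concern.** A ±50 ms window around a peak suits a component with a clear maximum inside a short search range. The LPP has a 600 ms range, and nothing in the plan says that its maximum will be sharp. Three difficulties follow.

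- **Execution.** The search range and the epoch end at the same point, so a late peak has no complete averaging window.
- **Comparability.** For standard stimuli the latency is tied to level and group, or to group and session. These are the factors compared afterwards. If the LPP is broad, the position of its maximum is largely noise, and two conditions may be scored on different parts of the response.
- **Circularity.** The window is placed where the study's own average is largest, and the same data are then tested against zero to decide whether the component is analysed at all.

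The LPP is one of four ERP components in both EEG stages, so the matter is limited in scope but recurs throughout the ERP analysis.

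**Working it through.** **Timing (document figures only).**
- Epoch end: 1,100 − 100 = 1,000 ms after onset.
- Latest peak with a full window: 1,000 − 50 = 950 ms.
- Part of the search range without a full window: (1,000 − 950)/(1,000 − 400) = 50/600 = 8.3%.
- Averaging window as a share of the LPP range: 100/600 = 16.7%.
- The stimulus onset asynchrony is 1,300 ms, so data to 1,050 ms exist before the next stimulus; they lie outside the epoch as defined.

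**Children per average.** In Stage 2 there are 40 per group and each child hears three of six blocks: 40 × 3/6 = 20 per level and group if balanced. In Stage 3 there are 18 per group.

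**How far the window can move.** If two conditions have no sharp peak and their latencies fall evenly and independently over 600 ms, the expected gap is 600/3 = 200 ms, and two 100 ms windows fail to overlap with probability (1 − 100/600)² = 69%. Simulation of two independent averages (1/f noise, exponent 0.5–2, 18–40 children; assumed) gave a mean gap of about 200–245 ms and no overlap in 68–74% of pairs. A flat LPP adds a constant and does not change this. Sessions share children, so the real drift may be smaller.

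**Bias and the test against zero.** The documents give no noise structure, so it is assumed throughout. In a single-channel simulation with no true LPP (500 Hz, baseline corrected; AR(1) time constant 20–200 ms or 1/f exponent 1–2; 1,000–1,500 studies per setting):
- Peak-centred score, n = 20: bias 0.11–0.16 SD of the simulated noise; rejection 6.2–10.4% at nominal 5%.
- Peak-centred score, n = 40: bias 0.07–0.12 SD; rejection 5.0–10.7%.
- Fixed 400–1,000 ms mean: bias −0.005 to +0.008 SD; rejection 4.1–5.8%.

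In standard errors, for example with n = 20 and a 20 ms time constant: 0.122/(0.672/√20) = 0.81.

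The plan takes latencies from all regions of interest, of which it lists 18. With 18 regions, n = 20 and no LPP, the result depends on how they are combined:

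| Latency taken from | Upward bias (SD) | Rejection at 5% | Peak after 950 ms |
|---|---|---|---|
| One channel | 0.13–0.16 | 6–9% | 10–13% |
| Peak of the all-region average | 0.07–0.13 | 5–8% | 8–15% |
| Mean of the regional peak latencies | 0.02–0.07 | 4–6% | 0–2% |

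The last two columns come from a separate run with 1/f exponents 0.5–1.5 and inter-region correlation 0.3–0.7. Its bias figures (0.12–0.15, 0.06–0.13 and 0.01–0.07) agree with those shown to within 0.01 SD.

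**The case against.** **The averaging over regions may remove most of the problem.** The words about all regions can be read as averaging the regional peak latencies. On that reading the bias is at most about 0.07 SD, the test against zero is close to nominal, and late peaks nearly vanish. This stands, and it is why the size must be given as a range. The text does not settle which reading applies.

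**The main comparisons are not shown to be inflated.** A reader might infer from the circular screen that the Group, Level and Session tests reject too often. The evidence does not support that. With 400 simulated pairs of groups and no true difference, the comparison rejected in 3–7% under all three latency rules. Simulation error alone gives 5% ± 1.96 × √(0.05 × 0.95/400), or about 2.9–7.1%. Withdrawals add little: halving the sample from 40 to 20 moved the single-channel bias by only 0.03–0.04 SD (for example 0.160 − 0.116 = 0.044), against a planning effect of d = 0.8.

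**The full window is not always more precise.** A reader might infer from the one-sixth share that the narrow window must be paid for with more children. In simulation the SD of a 100 ms mean was 1.07–1.29 times that of the 600 ms mean, but this is a loss only for a flat response. The documents place the LPP within the 400–1,000 ms window; they do not say it fills it. For an assumed bell-shaped LPP at 650 ms, height 0.8 SD, n = 20, power against zero was:

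| Width (SD) | Peak-centred | Full window |
|---|---|---|
| 80 ms | 70–81% | 20–22% |
| 150 ms | 80–88% | 49–54% |
| 250 ms | 84–92% | 76–80% |
| Flat | 94–98% | 92–94% |

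Selection flatters the peak-centred column somewhat, but cannot explain the first two rows. Dilution is therefore a real cost of the fixed window. With a localised LPP, late peaks occurred in only about 0–1% of runs.

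**The moving window is stated for standard stimuli only.** For deviants the plan names a grand mean latency without its source, so it cannot be said that the window moves there.

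**Conclusion.** The point holds as a specification fault with a cheap remedy. Two parts rest on the text alone: the rule is incomplete for peaks in the last 50 of 600 ms, and the latency for standard stimuli comes from averages defined by the factors later compared. That the comparisons then contrast different stretches of the response is conditional on the LPP having no sharp peak.

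The circularity of the test against zero is mild: about 0.02–0.16 SD of upward bias and about 4–10% rejection at nominal 5%, for about 20 children, no true LPP and assumed noise. With very slow noise, or with regional latencies averaged, it is small. It acts on the screen and should largely cancel in comparisons with equal numbers and noise.

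No claim about extra children needed is justified. Nor is the choice of voice for Stage 3 at risk, because the Stage 2 statistical analysis section bases it on the MMN.

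**What to change.** In the Stage 2 Data Analysis section and the Stage 3 ERPs section, add for the LPP only: amplitude is the mean over 400–1,000 ms after onset, without a peak search, identical for all levels, groups, sessions and stimulus types (standards and difference waves). Keep the ±50 ms rule for the MMN, P200 and P3a. The fixed window ends exactly at the epoch limit, so nothing runs over, and it removes both the data-driven placement and the movement between conditions.

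Because a response much narrower than 600 ms would be diluted, keep the peak-centred LPP as a sensitivity analysis. For that, state how latencies are combined over regions and which average supplies the latency for deviants, and either extend the epoch to at least 1,050 ms or limit the peak to 950 ms.

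The cost is a sentence or two in each section and a small change to the analysis code. No further data are needed.
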